Uptake and retention of participants in school-based intervention trials is a major issue that impacts the feasibility of future trials.^30^ This will be monitored through a mixed-methods evaluation encompassing quantitative and qualitative indicators. Quantitative indicators will include: a) comparisons of recruitment methods (for schools and then pupils into the study); b) successful data collection rates (low missing data); c) presence of floor/ceiling effects in collected data; d) whether responses on potential outcome measures remain static (or show ‘movement’) between baseline and follow-up; e) calculation of the precision of estimates of key parameters, which will inform a future trial. Qualitative indicators will include evaluation of the perceived mechanism of change and contextual factors impacting upon the effectiveness of the intervention for pupils and teachers. We will seek to interview participants who do not complete follow-up questionnaires to determine their reasons for not doing so and any factors that would improve completion rates. Factors that will determine stop/go procedures to a definitive trial will include: evidence that recruitment to a definitive study, using optimum recruitment pathways in one region, would be as follows: number of schools recruited at 9 months (6 excellent, 3-4 acceptable, 1-2 unacceptable), number of high-risk pupils recruited in the cluster-RCT per school (10-15 excellent, 5-10 acceptable, 0-5 unacceptable), and proportion of complete data collected (>80% acceptable). Retention will be judged by the following criteria: >80% completion excellent; 60-80% acceptable; below 60% unacceptable.

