**4.2 Progression Criteria**

A set of eight provisional progression criteria for the MAPSS programme have been established to determine whether a full RCT is warranted, and will be further developed in collaboration with the independent Trial Steering Committee (TSC; see Table 1). All progression criteria will need to be met for the MAPSS programme to be seen as acceptable and feasible, and to progress to a full efficacy trial.

*Table 1. Traffic light feasibility progression criteria*

| **Progression Criteria** | **Red**  **(stop)** | **Amber**  **(discuss and amend)** | **Green**  **(go)** |
| --- | --- | --- | --- |
| School recruitment (targeting n=6) | 1-2 schools recruited | 3-4 schools recruited | 6 schools recruited |
| Pupil participant recruitment (targeting n~810) | <20% of eligible pupils | 20-74% of eligible pupils | ≥75% of eligible pupils |
| School staff training recruitment | ≤2 teachers per school | 3-6 teachers per school | ≥6 teachers per school |
| Suicide Prevention workshop | <80% of scheduled workshops delivered | 80-99% of scheduled workshops delivered | 100% of scheduled workshops delivered |
| Pupils screening at high-risk of suicide | <5 pupils per school | 5-10 pupils per school | 10-15 pupils per school |
| Reframe IT-UK  Online CBT | <40% of eligible pupils engage with ≥75% of modules | 40-69% of eligible pupils engage with ≥75% of modules | ≥70% of eligible pupils engage with ≥75% of modules |
| Acceptability of intervention | <50% of pupils found MAPSS acceptable | 50-79% of pupils found MAPSS acceptable | ≥80% of pupils found MAPSS acceptable |
| Outcome data collected at baseline | Data collected from <50% of pupils | Data collected from 50-79% of pupils | Data collected from ≥80% of pupils |
| Follow-up outcome data attrition at T3 | >40% data attrition at T3 | 21-40% data attrition at T13 | ≤20% data attrition at T3 |

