**4.3 Planned intervention**

The training in schools for pupils, teachers, and parents will be funded by suicide prevention commissioners within the Local Authority (see Director of Public Health Letter).

1) A minimum of 6 staff from each school will receive training from Papyrus: **Suicide Prevention – Overview Tutorial (SP-OT)**, to ensure staff are equipped to manage any risk identified from the screening. SP-OT is delivered in a single session over 1.5 hours online. Papyrus will also provide an online information session, **Suicide Prevention - Awareness, Resource, Knowledge (SP-ARK),** along with support packs, for parents of all children in Year 10 at each participating school. #MyGPGuide; a guide for CYP with lived experience of self-harm and suicidality will be shared with schools and families.^31^

2) **Suicide prevention lesson** such as safeTALK, developed by LivingWorks Education,^32^ a suicide alertness training workshop suitable for anyone over the age of 14. The lesson comprises a single 3.5-hour face-to-face workshop, designed to help participants understand suicide warning signs in themselves and others, gain knowledge about sources of support, apply basic ‘TALK’ steps (Tell, Ask, Listen, and KeepSafe), and signpost others. Suicide prevention lessons will be delivered by trained Suicide Prevention Facilitators at Grassroots Suicide Prevention to classroom-sized groups of pupils (maximum 30 pupils per session with at least one teacher present).

3) The **screening** will take the form of self-report measures embedded into the questionnaires at each timepoint. Researchers will inform each school after each timepoint of any pupils who are assessed to be at risk. Pupils who report suicidal ideation within the past four weeks (Suicide Ideation Attributes Scale [SIDAS] score of 21 or higher)^33^ or any level of current suicidal ideation (single multiple-choice item) will be flagged by the research team and followed up by the school safeguarding lead.

4) **Reframe IT-UK** has been adapted from the Reframe-IT intervention developed in Australia.^17,27^ It comprises eight 20-minute online self-guided CBT modules, following the stories of two young people who make video diaries about their day-to-day life and their experience of feeling suicidal. There is also a message board through which the participants can communicate with a moderator, a mood diary, and signposting information.

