**4.8 Sampling**

To ensure a diverse range of schools and CYP are included in the feasibility trial, we propose purposeful maximum variation sampling. This is widely used in research to pragmatically identify and select participants that are effective in addressing the research aims, while also maximising diversity and limiting bias.^39^ The key characteristics we would seek variation on include: rural/urban status, proportion of ethnic minority pupils, schools’ deprivation levels (IDACI), schools’ academic achievement (proportion of pupils achieving benchmarks GCSE grades). To ensure we achieve this, we have allocated dedicated time in the project plan during the setup phase to collate school data (publicly available), approach and build relationships with schools who do not typically engage in research, and ensure buy-in from the senior leadership teams (via the collaborators). Both Principal Investigators have expertise in involving diverse communities in research programmes and have started this process during the pilot study.

*Sample size calculation:* As this is a feasibility study, a sample size calculation is not needed. In line with similar work,^26-28^ we will recruit 6 schools to provide sufficient variety of schools and pupil numbers in which to test recruitment, retention and acceptability of the intervention, and feasibility of the research design for evaluation. This is based on the assumption of a potential attrition rate of 50% at T3 (the primary outcome point for Reframe IT-UK). This is common for feasibility trials,^40^ realistic in terms of recruitment, and would allow adequate precision in estimating rates (e.g., attrition, adverse events) relevant to trial outcomes.^40^ This would allow an overall attrition rate of 50% to be estimated with 95% confidence intervals of +/- 12% or, 16% for a single arm. This sample size is also adequate for estimating relevant analysis parameters such as the standard deviation of effects, which are needed for determining the feasibility of a later efficacy trial.^40,41^ Based on findings from the pilot study, we anticipate that 10% of pupils will score in the at-risk range in the screening and will thus be eligible for Reframe IT-UK.

We will monitor recruitment rates from the different methods and associated costs by collecting data on:

1. The proportion of eligible young people who consented;

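### Table 1 gives some attainable results two colours (6 staff, 10 at-risk pupils) and others none (5 schools, more than 15 at-risk pupils), and does not say whether per-school criteria apply to every school or to the mean

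*Protocol*

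**What the plan says.** Protocol section 4.2 introduces Table 1 with "A set of eight provisional progression criteria for the MAPSS programme have been established". It adds that every criterion has to be met before a full trial, and that the set will be developed further with the TSC. The table has nine rows, each with a Red (stop), Amber (discuss and amend) and Green (go) cell. Three rows matter here:

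- School recruitment: "1-2 schools recruited | 3-4 schools recruited | 6 schools recruited".
- Staff training: "≤2 teachers per school | 3-6 teachers per school | ≥6 teachers per school".
- Pupils screening at high risk: Red is fewer than 5, and the Amber and Green cells are "5-10 pupils per school | 10-15 pupils per school".

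Section 4.1 gives stop/go factors in prose. It uses the same school bands and, for pupils, "number of high-risk pupils recruited in the cluster-RCT per school (10-15 excellent, 5-10 acceptable, 0-5 unacceptable".

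The planned values are stated elsewhere. Section 4.3 says "A minimum of 6 staff from each school will receive training from Papyrus". Section 4.6 plans about 810 pupils in six schools, with about 54 at-risk pupils in the four intervention schools and about 27 in the two control schools. Section 4.8 says "we anticipate that 10% of pupils will score in the at-risk range in the screening".

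**The concern.** The progression decision is the main product of a feasibility trial. A traffic-light table can support it only if each possible result falls in exactly one band. Here some results fall in two bands and others in none, and one of the doubly classified results is the number of staff the plan sets out to train.

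The pupil row has a second problem. With six schools there will be six counts, and the table does not say whether each must lie in the band or whether their average is judged. The upper limit of 15 makes this choice matter, because a school slightly above expectation leaves the Green band with no other band to enter.

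The all-criteria rule compounds this. It does not say whether an Amber result counts as met. If these points are still open when results arrive, the reading can be chosen with the results in view.

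**Working it through.** **1. Each whole number tested against the bands**

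| Criterion | Red | Amber | Green | In two bands | In no band |
|---|---|---|---|---|---|
| Schools (Table 1 and 4.1) | 1-2 | 3-4 | 6 | none | 0, 5 |
| Staff per school (Table 1) | ≤2 | 3-6 | ≥6 | 6 | none |
| At-risk pupils per school (Table 1) | <5 | 5-10 | 10-15 | 10 | 16 or more |
| At-risk pupils per school (4.1) | 0-5 | 5-10 | 10-15 | 5, 10 | 16 or more |

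Five at-risk pupils is Amber only in Table 1, but both acceptable and unacceptable in section 4.1. The two places also describe the count differently: pupils screening at high risk in Table 1, high-risk pupils recruited in section 4.1.

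**2. The plan's own expected counts**

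- Intervention arm: 540 × 0.10 = 54. Control arm: 270 × 0.10 = 27. Both match section 4.6.
- Per school: 810 / 6 = 135 pupils, and 135 × 0.10 = 13.5 at risk.

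**3. Every-school reading**

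Assume six equal schools and independent pupils, so that the count X in a school is Binomial(135, 0.10).

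- P(X > 15) = 0.274.
- P(X = 10) = 0.075.
- P(10 ≤ X ≤ 15) = 0.603.
- At least one of six schools above 15: 1 − (1 − 0.274)^6 ≈ 0.85.
- At least one of six at exactly 10 or above 15: 1 − (1 − 0.274 − 0.075)^6 ≈ 0.92.
- All six within 10-15: 0.603^6 ≈ 0.05.

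**4. Mean reading**

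Under the same assumptions the six-school total T is Binomial(810, 0.10).

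- Mean above 15 means T > 90: P = 0.134.
- Mean above 10 and up to 15 (Green only) means 61 ≤ T ≤ 90: P = 0.860.
- Mean exactly 10 means T = 60: P = 0.002.

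**5. Sensitivity, using assumed values the protocol does not give**

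- At-risk rate 8% / 12% / 15%: P(X > 15) in one school = 0.07 / 0.56 / 0.88. At 12% the mean exceeds 15 with probability 0.76.
- Intraclass correlation 0.01 to 0.05 at a 10% rate (beta-binomial): P(X > 15) = 0.33 to 0.35, at least one of six above 15 = 0.91 to 0.92, and all six within 10-15 below 0.01.

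**The case against.** **The criteria are provisional.** Section 4.2 says so and promises further work with the TSC. That lowers the stakes, because there is a route to correct them. It does not resolve the bands: the all-criteria rule is already stated on them, and no date is given by which they must be final.

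**On the sensible reading the pupil row mostly works.** If the mean is meant, about 86% of outcomes are clearly Green under the plan's own figures. This stands, and it means the 0.85 and 0.05 figures must not be quoted without their condition. They apply only if every school has to lie in the band. The protocol does not choose between the readings.

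**The faults are not all at the planned results.** A reader might infer that the bands fail at the values the plan expects throughout. That is true only of 6 staff. Six schools and 13.5 at-risk pupils are each Green and nothing else. Ten pupils, more than 15 pupils and five schools are possible results, not planned ones, although a school above 15 is likely. A reader might also note that 75% pupil recruitment gives 0.75 × 810 × 0.10 / 6 = 10.1 per school and call this the overlap. It is not: the overlap is exactly 10, and 10.1 is Green.

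**Amber and safety.** Amber followed by an agreed amendment could be read as met, so the all-criteria sentence is unclear, not contradictory. The lack of a safety row in Table 1 is a design choice. Safety is operationalised in section 4.1 and overseen under section 4.14, so its absence from the table is not an error.

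**These are only boundary edits.** They change no randomisation, estimate or data collection. That is correct, and it is why the correction is cheap.

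**Conclusion.** The point holds as a defect in stated decision thresholds. Table 1 classifies 6 staff and 10 at-risk pupils twice, and leaves 5 schools and more than 15 at-risk pupils unclassified. Section 4.1 repeats the school gap, the overlap at 10 and the cap at 15, and conflicts with Table 1 at 5 pupils. These are not extraction faults, because the school and pupil bands appear both in the table and in prose. Nor is this a matter left to an analysis plan, since the protocol fixes the thresholds itself.

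The practical size depends mainly on the undefined per-school rule. With results running to plan, all six schools fall within 10-15 about 5% of the time, whereas the mean is clearly Green about 86% of the time. These figures rest on equal schools of 135, full recruitment, a 10% rate and independent pupils. Schools are deliberately sampled for variety, so real counts will probably spread more widely. The count of eight criteria against nine rows is a minor slip.

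**What to change.** Revise Table 1 and the matching sentence in section 4.1 together, with TSC sign-off before outcome data are seen. One workable version:

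- Schools: 0-2 / 3-5 / 6 or more. The Green band should be open at the top because section 11 allows more sites to be added if recruitment is slow.
- Staff: 2 or fewer / 3-5 / 6 or more, stated as applying in each school.
- At-risk pupils: mean per school below 5 / at least 5 and below 10 / at least 10. Cut-points must be continuous if a mean is used. Whole-number bands of 5-9 and 10 or more would leave a six-school mean such as 9.5 without a colour. At 75% recruitment (about 607 pupils) the chance of a mean strictly between 9 and 10 is about 0.24, from Binomial(607, 0.10) totals of 55 to 59.
- Give counts above 15 a separate colour only if 15 is meant as a capacity limit, and say so.

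Also state whether the pupil criterion counts those screening at high risk or those recruited, state whether Amber counts as met under the all-criteria rule, and change eight criteria to nine.

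The cost is a table edit, a few sentences and one committee approval. Nothing changes in recruitment, randomisation or data collection.

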**4.3 Planned intervention**

The training in schools for pupils, teachers, and parents will be funded by suicide prevention commissioners within the Local Authority (see Director of Public Health Letter).

1) A minimum of 6 staff from each school will receive training from Papyrus: **Suicide Prevention – Overview Tutorial (SP-OT)**, to ensure staff are equipped to manage any risk identified from the screening. SP-OT is delivered in a single session over 1.5 hours online. Papyrus will also provide an online information session, **Suicide Prevention - Awareness, Resource, Knowledge (SP-ARK),** along with support packs, for parents of all children in Year 10 at each participating school. #MyGPGuide; a guide for CYP with lived experience of self-harm and suicidality will be shared with schools and families.^31^

2) **Suicide prevention lesson** such as safeTALK, developed by LivingWorks Education,^32^ a suicide alertness training workshop suitable for anyone over the age of 14. The lesson comprises a single 3.5-hour face-to-face workshop, designed to help participants understand suicide warning signs in themselves and others, gain knowledge about sources of support, apply basic ‘TALK’ steps (Tell, Ask, Listen, and KeepSafe), and signpost others. Suicide prevention lessons will be delivered by trained Suicide Prevention Facilitators at Grassroots Suicide Prevention to classroom-sized groups of pupils (maximum 30 pupils per session with at least one teacher present).

3) The **screening** will take the form of self-report measures embedded into the questionnaires at each timepoint. Researchers will inform each school after each timepoint of any pupils who are assessed to be at risk. Pupils who report suicidal ideation within the past four weeks (Suicide Ideation Attributes Scale [SIDAS] score of 21 or higher)^33^ or any level of current suicidal ideation (single multiple-choice item) will be flagged by the research team and followed up by the school safeguarding lead.

4) **Reframe IT-UK** has been adapted from the Reframe-IT intervention developed in Australia.^17,27^ It comprises eight 20-minute online self-guided CBT modules, following the stories of two young people who make video diaries about their day-to-day life and their experience of feeling suicidal. There is also a message board through which the participants can communicate with a moderator, a mood diary, and signposting information.

**4.4 Control/Comparator Group**

Participants in schools randomised to the control group will receive treatment as usual (TAU; e.g., from the school nurse or external mental health services), based on the typical provision at each school. The pastoral staff will be asked to record what TAU comprises in each school through the completion of a ‘usual practice’ survey prior to randomisation and at T4, to establish programme differentiation, any changes over time, and to control for any compensatory rivalry that may occur over the course of the trial. To ensure safety and appropriate support in the event of pupils being flagged as at-risk in the control group, schools who do not engage with the SP-OT (suicide prevention training for designated teachers in recruited schools) training will be unable to progress through the trial.

**4.5 Setting/Context**

Mainstream secondary schools and Pupil Referral Units (PRU) in Northwest England will be approached to participate. Papyrus’ SP-OT training for teachers will be delivered in all schools. The suicide prevention lesson will be delivered in all 6 schools (4 in the intervention arms and 2 in the control arm after the trial is complete, *if deemed safe*), in typical classroom settings. Pupils participating in Reframe IT-UK in the 4 intervention schools will complete the modules online during school time, in the presence of a pastoral member of staff, with the option of accessing additional resources during their own time. A guidance pack for schools will is being developed in collaboration with Headteacher Co-Is (SY) and a manual will be provided for Reframe IT-UK. The guidance will be provided to participating schools and will advise them of key information, including project timelines and milestones, their role and responsibilities, and young people’s rights throughout the project (including the importance of safeguarding and confidentiality). It will also include information on supporting staff wellbeing.

**4.6 Study Population**

Participants will include Year 10 pupils (aged 14-15). Opt-out ethical procedures will be used – these have been approved by the university research ethics committee in the pilot study and were acceptable to parents and schools. We will utilise purposeful maximum variation sampling to recruit schools in different areas across the region and to ensure inclusivity of diverse populations (e.g., rural/urban, ethnic minority groups, differing deprivation levels, differing academic achievement levels). We will work with partners across the region who can support with this (e.g., Papyrus, Cheshire and Merseyside Safeguarding Group).

The sample will consist of ~810 adolescent pupils in Year 10, recruited from 6 mainstream secondary schools across Cheshire and Merseyside. Six schools will be randomly assigned to one of two arms as part of a cluster-RCT: intervention (n=4) or control arm (n=2). Year 10 pupils in the intervention schools will receive: 1) suicide prevention lesson (n~540 pupils); and 2) pupils scoring 21 or above on the SIDAS^33^ or indicating past suicide ideation will also be offered Reframe IT-UK plus TAU (n~54 pupils). Those in the control arm will receive TAU only (n~27 pupils).

**4.7 Overview of Research Methods**

***Quantitative Data Collection***

Participants will complete a suite of quantitative measures (see details below) online in school at 4 time-points: baseline (T1); 2-4 weeks post-baseline (after suicide prevention lesson; T2); 12 weeks post-baseline (after Reframe IT-UK; T3); and 1-year post-baseline (T4). The survey system will flag participants who score in the at-risk range for suicidal ideation.^33^ The research team will then contact the school about these pupils to determine eligibility for participation in the Reframe IT-UK in intervention schools. Eligible pupils will then be offered the intervention and TAU. Pupils receiving the Reframe IT-UK intervention will complete the 8 modules in the 10 weeks between T2 and T3 (i.e., approximately one module per week). Primary outcomes will be measured at T2 for suicide prevention lesson and T4 for Reframe IT-UK.

***Qualitative Process Evaluation***

We will conduct longitudinal case studies of the 4 schools randomised to receive MAPSS. The case studies will explore inter-related issues of 1) social validity of MAPSS and 2) *how* MAPSS was implemented and *why* it was implemented in this way. In terms of social validity, we will utilise Wolf’s framework,^34^ focusing on key tenets of acceptability, feasibility, and utility (e.g., does the intervention meet schools’ perceived needs? How well received is the intervention among staff and pupils? Can the intervention be delivered successfully?). Here we will draw upon relevant studies of school-based interventions (e.g., Kendal, et al)^35^ and adapt existing rubrics from the implementation literature (e.g., Bird et al)^36^ to inform our data generation.

In terms of how MAPSS was implemented, we will focus on the following dimensions: fidelity (e.g., to what extent teachers adhered to MAPSS guidance), dosage (e.g., how much of MAPSS pupils accessed), quality (e.g., how well MAPSS was delivered), participant responsiveness (e.g., the extent to which pupils engaged), reach (e.g., the rate and scope of participation), programme differentiation (e.g., to what extent MAPSS can be distinguished from other, existing mental health programmes), and adaptations (e.g., the nature and extent of changes made during implementation). We will also explore a range of factors that may have affected implementation at the different domains/levels consistently: preplanning and foundations (e.g. buy-in), implementation support system (e.g. ongoing external support), implementation environment (e.g. time constraints), implementer factors (e.g. experiences, skills and confidence in delivery), and programme characteristics (e.g. flexibility).^36-38^

***Methods for Sharing Study Progress and Findings with Participants and Payments, Rewards and Recognition for Participants***

Each participating school will be invited to nominate a minimum of 6 key staff members to complete SP-OT training delivered by Papyrus, to increase staff capacity to enact safety protocols, and to act as an incentive for schools to participate. To ensure safety and appropriate support in the event of pupils being flagged as at-risk, schools who do not engage with the SP-OT training will be unable to progress through the trial.

Upon completion of the study, schools will be provided with an anonymised aggregate report of the questionnaire data collected to encourage retention and to recognise the time they have given to the study. Schools will also be provided with a certificate of participation.

